### Interventions

Across the 14-week duration of the trial, participants will be first allocated to a six-week WBV intervention, a two-week washout period [37], and a six-week PLACEBO intervention.

### WBV intervention

The WBV intervention will consist 12 WBV sessions over a consecutive six-week period. The participants will complete two vibration sessions per week separated by at least 48 hours. Efficacy of session frequency had been previously established for healthy community-dwelling older adults [25]. A WBV session will consist of five, 60 second vibration bouts, interspersed with 60 seconds of passive rest. Although the most effective protocol is yet to be established, the selected protocol had been used previously to establish efficacy of WBV interventions [36,38,39]. During rest, the participant will remain on the vibration platform and will be encouraged to stand with a posture that resembles the ‘anatomical position’. More specifically, the participant assumes a standing position with the feet together, the arms to the side, and the head, eyes and palms facing forwards. The forearms are supinated.

A side alternating vibration platform (Amazing Super Health, Melbourne, AUS) will be used. For each vibration bout, platform frequency will be 25 Hz, peak-to-peak displacement 2.0 mm, peak acceleration ~24.67 m.s^-2^, and gravitational force ~2.52 *g*. The WBV intensity was chosen to reduce the risk of fracture to fragile bones [40] and potential for other injury [41]. The vibration platform peak-to-peak displacement and frequency were validated prior to this proposal in an unpublished pilot study. Foot placement (second toe) will be equidistant, 20 cm from axis of rotation. The participant will wear flat soled shoes. Skidding will be checked according to the recommended method of the International Society of Musculoskeletal and Neuronal Interactions. A piece of paper will be placed under the foot during a vibration bout to ensure constant contact with the vibration platform [42]. The participant will be required to stand with ~20º knee flexion to allow transmission of vibration about the lower limbs [43]. Knee angle will be filmed, and later quantified across the intervention for each participant.

### PLACEBO intervention

A prototype vibration platform will be used for the PLACEBO intervention. For each vibration bout, platform frequency will be 25 Hz, peak-to-peak displacement ~0.0 mm, peak acceleration ~0.00 m.s^-2^, and gravitational force ~0.0 *g* (cognisant that the Earth’s gravitational force is constant 1.0 *g*). Participants will be required to follow the same procedure of the WBV intervention. Participants will be told the PLACEBO intervention is an “ultra-low frequency” vibration intervention that is “very different” to the aforementioned WBV intervention.

### Outcome measures

Reliability of outcome measures will be established over a test-retest-retest protocol. Exercise tolerance variables will be immediate responses to WBV; (1) perceived dyspnoea quantified with the Borg CR-10 visual analogue scale, (2) heart rate, and (3) saturation of haemoglobin. Functional performance variables will be simulated ADLs and kinematic markers of gait; (1) the 5-chair stands test, (2) the timed up and go test, (3) stride length, (4) stride time, and (5) stride velocity. Data will be collected at baseline and subsequent fortnight for 14 weeks. Data of all dependent variables will be collected to quantify at least one of three different data classifications: (1) immediate, (2) acute, and (3) long-term. Immediate perceived dyspnoea, heart rate, and saturation of haemoglobin will be collected during the final WBV or PLACEBO bout (after 30 seconds of the 60 second bout). Acute kinematic markers of gait will be collected within two minutes of a completed WBV or PLACEBO bout [38,44]. Long-term simulated ADLs and kinematic markers of gait will be collected at least 48 hours after a WBV or PLACEBO bout [25,45].

To complete the 5-chair stands test the participant is asked to sit in a standard height (46 cm, including back rest) chair with arms folded across the chest. The participant is then asked to stand and sit five times [35,46].

To complete the timed up and go test, the participant is asked to sit in a standard height (46 cm) arm (63 cm) chair. The participant is then asked to stand, walk three metres to a marker on the floor, turn, return, and sit on the chair [46,47].

Kinematic markers of gait will be quantified with the GAITRite® electronic walkway (CIR Systems Inc, Peekskill, USA). Participants will be instructed to walk at a self-selected comfortable speed along a straight, flat, and even walkway area containing the mat. Body length is measured from the base of the foot (unshod) to the crown of the head while standing in the anatomical position. During data collection, participants will walk (shod) over the mat five times in a discontinuous process with an approach and departure distance equal to two body lengths. The procedure was reliable for step length, step time, and velocity among older woman (ICC range 0.860 to 0.940; mean age = 68 years) [48].

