## Methods/design

This trial will be conducted as a non-randomised intervention with crossover to placebo. Given the nature of COPD, and exacerbations expected of it, this trial will be a phase II efficacy trial and as such will not be conducted as a randomised controlled trial. People with stable COPD will be invited to participate. It is necessary to first conduct the WBV intervention, and then the PLACEBO intervention in an effort to maximise participant numbers in the WBV group, with anticipated dropout over the course of the 14-week intervention. A control condition could compromise trial compliance and randomisation is not critical to an efficacy trial.

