### Sample size

It is expected that WBV will not change dyspnoea from baseline. To allow sample size calculation therefore, data of functional performance variables were considered primary and used to estimate sample size. The selected dependent variables were sourced from a previous study of WBV and healthy community-dwelling older adults [25]. Sample size needed for a one tailed paired *t*-test with α 0.05 and *n* = 14 with power = 0.90 was *n* =16 for the 5 chair stands test *n* < 10 for the timed up and go test. To allow for an anticipated participant drop out of at least 20%, a total of 20 participants will be included in the study.

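### The baseline test is not tied to the planned test-retest-retest, so with WBV always first, practice on the 5-chair stands and timed up and go tests may be read as a WBV effect

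*Protocol article*

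**What the plan says.** - **Repeat tests** (Outcome measures): "Reliability of outcome measures will be established over a test-retest-retest protocol". Reliability is the only stated purpose. The section does not say whether enrolled participants do the three tests, when they take place, or which result is the baseline. No familiarisation trial is named for the 5-chair stands or timed up and go tests.
- **Schedule** (Outcome measures): "Data will be collected at baseline and subsequent fortnight for 14 weeks".
- **Order** (Interventions): "participants will be first allocated to a six-week WBV intervention, a two-week washout period [37], and a six-week PLACEBO intervention". Methods/design confirms it: "This trial will be conducted as a non-randomised intervention with crossover to placebo". The reason given is "It is necessary to first conduct the WBV intervention, and then the PLACEBO intervention in an effort to maximise participant numbers in the WBV group". No participant has the opposite order, and there is no parallel control.
- **Primary outcomes and sizing** (Sample size): "data of functional performance variables were considered primary and used to estimate sample size". The two outcomes used for sizing are the 5-chair stands and timed up and go tests. The calculation starts "Sample size needed for a one tailed paired *t*-test with α 0.05", with power 0.90. It gives 16 for the chair stands and fewer than 10 for the up and go, and the total is set at 20 to allow for dropout.

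**The concern.** The two sizing outcomes are effort-dependent performance tests, on which people may improve over the first few attempts simply by repeating them. With a fixed order, such a gain is not balanced across the two conditions. The tests at weeks 2, 4 and 6 follow the baseline and belong to WBV. The week-8 test that opens PLACEBO is already the fifth on the fortnightly schedule.

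Practice and a WBV benefit point the same way. Because nobody takes the conditions in reverse order, no later analysis can separate them, so the protection has to come before the first WBV session. The protocol already plans three repeats that could provide it, but does not assign them to that purpose.

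**Working it through.** **1. The plan's own figure.** No effect size or SD is given, so n = 16 cannot be derived forwards. Solving backwards with the noncentral t (one-sided paired test, alpha 0.05, power 0.90), n = 16 corresponds to a standardised paired effect of about 0.77 to 0.80. The dropout step reproduces: 16 / (1 − 0.20) = 20.

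**2. False-positive rate under practice alone.** Suppose WBV has no effect and practice shifts the mean of the tested paired difference by δ, in SDs of that difference. The rate is P(T > t with n − 1 df at 0.95), where T is noncentral t with n − 1 df and noncentrality δ√n. At n = 16, √n = 4. The values of δ are assumptions.

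| δ | δ / 0.767 | n = 16 | n = 20 |
|---|---|---|---|
| 0 | 0 | 0.050 | 0.050 |
| 0.1 | 0.13 | 0.103 | 0.112 |
| 0.2 | 0.26 | 0.189 | 0.217 |
| 0.3 | 0.39 | 0.309 | 0.363 |
| 0.4 | 0.52 | 0.453 | 0.532 |

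A shift about a quarter of the effect implied by the sizing (δ = 0.2) nearly quadruples the nominal error.

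**3. How much PLACEBO cancels, and how much a later baseline helps.** This is an illustrative curve, not taken from the documents. After k earlier tests the practice gain is g(1 − r^k), with total g = 0.5 SD and r the share of the remaining gain left after each test. The baseline has b earlier tests: b = 0 if it is the first test, b = 2 if it is the third.

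- WBV-period gain: g(r^b − r^(b+3)).
- PLACEBO-period gain, from the week-8 test to week 14: g(r^(b+4) − r^(b+7)), which is r^4 times the WBV-period gain.
- PLACEBO therefore cancels a share r^4 of the bias: 0.3^4 = 0.8%, 0.5^4 = 6%, 0.7^4 = 24%.
- Moving the baseline from the first to the third test multiplies the bias by r^2: 0.09, 0.25 or 0.49.

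Gains below are fractions of g. The last column is the false-positive rate for WBV change minus PLACEBO change at n = 16.

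| Baseline | r | WBV gain | PLACEBO gain | Difference | Rate |
|---|---|---|---|---|---|
| First test | 0.3 | 0.973 | 0.008 | 0.965 | 0.578 |
| First test | 0.5 | 0.875 | 0.055 | 0.820 | 0.469 |
| First test | 0.7 | 0.657 | 0.158 | 0.499 | 0.245 |
| Third test | 0.3 | 0.088 | 0.001 | 0.087 | 0.070 |
| Third test | 0.5 | 0.219 | 0.014 | 0.205 | 0.105 |
| Third test | 0.7 | 0.322 | 0.077 | 0.245 | 0.120 |

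If the contrast is instead WBV change from baseline alone, the rates are 0.584, 0.510 and 0.348 with the first test as baseline, and 0.070, 0.110 and 0.152 with the third.

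**4. Averaging two baseline tests.** With error variance e per test, the error part of a change score is e + e = 2e for a single baseline and e + e/2 = 1.5e for the mean of two. The reduction is 0.5/2 = 25%. It does not apply if the third test alone is used.

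**The case against.** The article is silent on the baseline; it does not rule out using the repeats. A reader might infer from the reliability sentence that the repeats are kept away from the baseline and that practice therefore does fall in the WBV period. The text does not support that. If participants do all three tests before the first WBV session and the last is the baseline, most of the safeguard may already exist. A condensed article may also leave such details to the full protocol. This stands, and it makes the harm conditional. It does not dispose of the point, because the fixed order, the defence of not randomising and the stated purpose of the repeats are all in this text, and it is their combination that creates the exposure.

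Three other strong readings also go beyond the documents:

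- **That learning is complete by week 8, so PLACEBO cancels nothing.** No learning curve is given. In the slow-learning illustration PLACEBO removes about a quarter of the bias.
- **That the trial will declare practice to be efficacy through a one-tailed test.** The one-tailed paired t-test is stated for sizing only, and the contrast is not named. The direction argued here holds for change from baseline, or for a comparison of changes between periods. It would not hold for a direct comparison of end-of-period values, where the later PLACEBO measurements are the more practised.
- **That the same applies to gait.** Gait is walked at the participant's own pace, five times per collection. The practice argument is made for the two performance tests only.

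It is also fair to say that the root problem is the fixed, non-randomised order. Choosing a better baseline mitigates one consequence of it.

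**Conclusion.** The point holds in conditional form. The article ties its three repeat tests only to reliability and does not identify the baseline test. With WBV first for everyone, practice after that baseline falls mainly in the WBV period. The resulting bias favours WBV if the first test is the baseline, or if the repeats are done in other people or later, and if the analysis uses changes from baseline.

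The size rests wholly on assumption, since neither the existence nor the amount of practice is documented. Shifts of 0.1 to 0.4 SD in the tested contrast give false-positive rates of 10% to 45% at n = 16. On the illustrative curves, using the third test as baseline lowers the WBV-minus-PLACEBO rate from 24–58% to 7–12%. That is a worthwhile gain at little cost, but not a cure. This is a cheap improvement to the design as fixed, not an established error in it.

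**What to change.** Under Outcome measures:

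1. State that all enrolled participants complete the test-retest-retest of the 5-chair stands and timed up and go tests before the first WBV session.
2. Treat the first test as familiarisation, and name the third test, or the mean of the second and third, as the week-0 baseline for these two outcomes. Choose one in advance; only the mean brings the 25% cut in the error part of the change score.
3. Report the first-to-third change as the trial's own estimate of practice.
4. Acknowledge that residual practice and other period effects remain confounded with treatment under the fixed order.

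If the repeats are already planned in participants before WBV, this costs a few sentences. Otherwise it adds at most two short repeat tests per participant, with the same equipment.

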### Objective

The objective of the trial is to advance knowledge of effects of physical activity on exercise tolerance and functional performance of the lower limbs of people with COPD, and to test the efficacy of a WBV intervention to beneficially effect exercise tolerance and functional performance of the lower limbs without causing exacerbations. The intervention will be conducted and data collected in the home of each participant.

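### Exercise tolerance is measured only during the vibration or sham bout, where the stimulus differs, so these readings cannot show whether training improved it

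*Protocol article*

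**What the plan says.** The Objective section of the protocol article sets the aim "to test the efficacy of a WBV intervention to beneficially effect exercise tolerance and functional performance of the lower limbs without causing exacerbations". Exercise tolerance is one of its two efficacy targets.

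Outcome measures then defines the construct: "Exercise tolerance variables will be immediate responses to WBV". The three variables are Borg CR-10 dyspnoea, heart rate and haemoglobin saturation. On timing it says "Immediate perceived dyspnoea, heart rate, and saturation of haemoglobin will be collected during the final WBV or PLACEBO bout", at 30 seconds into a 60-second bout.

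The other two classes of data contain none of these variables:

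- Acute: "Acute kinematic markers of gait will be collected within two minutes of a completed WBV or PLACEBO bout".
- Long-term: "Long-term simulated ADLs and kinematic markers of gait will be collected at least 48 hours after a WBV or PLACEBO bout".

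Simulated ADLs and gait are classified in the same section as functional performance, not exercise tolerance.

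The WBV intervention section gives 25 Hz, 2.0 mm peak-to-peak, about 24.67 m/s² and about 2.52 g. The PLACEBO intervention section gives "peak-to-peak displacement ~0.0 mm, peak acceleration ~0.00 m.s^-2" (m/s²), with the procedure otherwise the same. The Sample size section expects no change in dyspnoea and treats functional performance as primary.

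**The concern.** The article's Background presents better exercise tolerance as an adaptation to activity continued over time, with benefit for daily tasks. To detect that, one needs the response to a comparable effort before and after training, in both conditions. Readings taken inside the bout show how demanding that bout is, and the bout itself differs between the two periods.

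At stake is one of the two named efficacy aims. Higher, lower or equal heart rate and dyspnoea under WBV could each be reported as a finding on exercise tolerance, and none would identify a training effect. No analysis plan can repair this afterwards, because analysis cannot supply a reading under a common load that was never taken.

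**Working it through.** **1. Reproduce the stated stimulus.** Inputs from WBV intervention: frequency f = 25 Hz; peak-to-peak displacement 2.0 mm, so amplitude A = 2.0/2 = 1.0 mm = 0.001 m.

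Peak acceleration = (2πf)² × A = (2π × 25)² × 0.001 = 24.67 m/s². Divided by 9.81 this is 2.52 g. Both figures match the article.

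PLACEBO: A ≈ 0, so peak acceleration = (2π × 25)² × 0 = 0 m/s², also as stated.

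**2. Which variables are read under which load.**

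| Class | Variables | Load at reading |
|---|---|---|
| Immediate | dyspnoea, heart rate, saturation | 2.52 g in WBV, 0 g in PLACEBO |
| Acute | gait | off the platform, shortly after a bout |
| Long-term | simulated ADLs, gait | off the platform, 48 hours or more after a bout |

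Every exercise-tolerance variable is in the first row. None is read under a load common to both periods.

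**3. What the between-condition difference contains.** Write Y(load, state) for a reading, with load v (vibration) or 0, and state W (after WBV training) or P (after PLACEBO). The observable difference is

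Y(v, W) − Y(0, P) = [Y(v, W) − Y(0, W)] + [Y(0, W) − Y(0, P)].

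The first bracket is the acute response to vibration. The second is the training effect, together with any period effect, since WBV always comes first. Y(0, W) is not planned, so one observed difference has to cover separate components that it cannot distinguish.

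**4. What the within-period trend contains.** The WBV bout is fixed in frequency, displacement, posture and duration, so fortnightly readings in that period are repeated responses to one load. A fall could reflect adaptation. It could also reflect familiarity with the device or the passage of time, and no PLACEBO reading exists at load v to separate these. Setting the WBV trend against the PLACEBO trend does not solve this, because the two trends are observed at different loads and in a fixed order.

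**5. What is untouched.** The Sample size section sizes on the 5-chair stands test: 16/(1 − 0.20) = 20, as stated. Neither that test nor the timed up and go is read on the platform, so the point does not reach the primary variables or the sample size.

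**6. Whether the repair fits the schedule.** WBV runs from week 0 to 6, washout from 6 to 8, PLACEBO from 8 to 14 (6 + 2 + 6 = 14). Fortnightly collection from baseline gives weeks 0, 2, 4, 6, 8, 10, 12 and 14, which include the start and end of each period.

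**The case against.** The strongest reply is that the in-bout contrast answers a question the trial does ask. The Background looks for activity that keeps dyspnoea low, and the Discussion asks whether WBV will be well tolerated. For that acute question a sham that differs only in vibration is the right comparator, and the article openly calls these variables immediate responses. This stands, and it is why the readings should be kept under another label. It does not rescue the efficacy aim, which has no other measure.

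Four stronger readings are tempting, and the article does not support them.

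- *That the whole objective fails.* Functional performance is primary and is tested off the platform, so only the exercise-tolerance half is affected.
- *That the bias runs against WBV, with a size set by 2.52 g against 0 g.* Those figures are platform acceleration, not participant workload. Posture, bouts and rests are the same in both conditions. The article reports no heart rate, dyspnoea or saturation response to this stimulus in COPD, and it expects dyspnoea not to change. Neither direction nor size can be derived.
- *That change from baseline is undefined because no bout has been performed at baseline or week 8.* The article says data are collected at baseline but not under what condition. A rest reading, a familiarisation bout or a reliability session are all possible, and a condensed article may leave this to the full protocol.
- *That the in-bout readings contain no information on adaptation.* The constant-load trend within the WBV period contains some. Its weakness is the missing control.

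It is also fair to object that readings after chair stands or timed up and go would not be at identical workload: if WBV speeds performance, the work is done at a higher rate. That is right, and it shapes the fix.

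**Conclusion.** The point holds for the exercise-tolerance half of the objective. All three of its variables are read only under a stimulus that differs between conditions, so a WBV-versus-PLACEBO difference cannot be attributed to training, and the WBV-period trend is uncontrolled. The primary functional outcomes and the sample size of 20 are not affected, and no direction or magnitude of bias can be stated.

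Two assumptions underlie this. First, the listed measures are the complete set for exercise tolerance; the article's definition reads that way. Second, the variables are meant to be compared between WBV and PLACEBO. The article does not spell out that analysis, but the crossover to placebo and the parallel collection in both kinds of bout imply it. The defect lies in what is measured, so it has to be settled before data collection.

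**What to change.** 1. Relabel the in-bout dyspnoea, heart rate and saturation as immediate response to, or tolerability of, the bout. Draw no exercise-tolerance efficacy claim from them. State the condition under which their baseline reading is taken.

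2. Record Borg score, heart rate and saturation at the end of the 5-chair stands test (or the timed up and go) at the long-term assessments at weeks 0, 6, 8 and 14. The relevant contrast is the change from week 0 to 6 against the change from week 8 to 14 within each participant.

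3. Report these readings alongside the test time, because the task is fixed but the pace is not, and limit any exercise-tolerance claim to that task.

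4. If this is not wanted, drop the exercise-tolerance efficacy aim from the Objective and keep functional performance and tolerability.

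Cost: about one or two minutes per existing visit with devices already in use, protocol wording, and a narrower claim. This assumes the functional tests are performed at those four visits, as the fortnightly schedule suggests. It gives both periods a common task but does not remove the fixed WBV-first order. The article also gives no figure for how far such short tests raise the three readings, so their sensitivity is unknown.
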